**2. Exclusion criteria**

1. Pregnant or lactating females；
2. Prior history of malignancies, other than breast cancer；
3. Having participated in a prior investigational study within 1 months prior to Day 1 dosing；
4. Uncontrolled intercurrent illness；
5. Known sensitivity or allergy to PA-MSHA；
6. Unwilling or unable to comply the protocol；
7. Any other condition that investigator think the subject is not suitable for the study.

**IV.Treatment**

PA-MSHA 1 mg was administered subcutaneously every other day and capecitabine 1000 mg/m2 orally twice a day for 2 weeks on, 1 week off. The patient may continue treatment until unacceptable toxicities, disease progression.

**V. Assessment types**

**1 Efficacy assessment**

The response to treatment should be assessed by investigator based on RECIST version1.1 every two cycles.

**2. Safety assessment**

Safety will be monitored by assessing physical examination, performance status and laboratory examinations. Adverse events will be recorded based on CTC-AE version 3.0.

**VI Study procedure**

**1. Screening**

1. Patients information collection included Her-2, ER, PR status, Demography, Diagnosis and extent of cancer, relevant medical history, prior anti-cancer treatment；
2. Physical examination：including vital signs；
3. Hematology laboratory assessment（RBC、WBC、PLT、Hb）
4. Urinalysis（PRO、WBC、RBC）
5. ECG
6. Chemistry laboratory assessment（TP、TBIL、ALT、AST、AKP、A/G、LDH、 BUN、Cr）
7. Tumor assessment：chest CT、abdominal MRI、bone scan, ect.
8. Immunology assessment（CD3、CD4/CD8、NK、IL-2、IFN-γ、IL-4、IL-10 MMP-9、VEGF、E-Cadherin）
9. ECOG performance status.

**2. During treatment**

Laboratory assessment, physical examination and ECOG performance status will be assessed at the beginning of every cycle.

Chest CT、abdominal MRI and CEA、CA15-3、CA125 will be done every two cycles.

**VII. Concomitant medications and procedures**

**1. Hormonal therapy**

Concomitant hormonal therapy is not permitted.

**2. Biphosphonates**

Concomitant bisphosphonates is permitted if renal function is normal.

**3. Palliative radiation therapy**

Palliative radiation therapy in aim of relieving pain is permitted.

**4. Supportive care**

Supportive care including G-CSF, platelet transfusion and IL-11 is permitted.

All the concomitant drugs should be recorded in CRF.

**VIII. Study endpoints**

**1. primary endpoint：**progression free survival（PFS）

**2. 次要终点：**objective response rate（ORR）、overall survival（OS）、safety、immune index

**IX Usage method and precaution**

**Xeloda**

Drug administration are allowed to delay for 3 weeks in order to allow the toxicity to recover to baseline levels or grade 0~1. However, the dose of capecitabine should be reduced only in the event of severe toxic effects, including: adverse events ≥2 grade 2, such as diarrhea, persistent nausea/vomiting though given preventive measures, hand-foot syndrome (HFS), or elevated liver enzymes (AST and ALT > 2.5×ULN).

Once the patients decrease the dose of capecitabine, the dose will not be increased in the later cycles. But if the administration is interrupted and causes the treatment absence, the later treatment should continue to follow the schedule as planned, and the dose missing due to interruption of treatment should be made up. In addition, if the rest period extended over the next treatment cycle, capecitabine should be given a full dose of 14 days at restart of treatment and the treatment schedule shall be carried out as planned.

Please refer to appendix 5 for the standard dose according to body surface area and dose reduction of capecitabine.

Administration instructions

- Capecitabine of 1000 mg/m2 is given twice every day, from the first day to the 14th day in the cycle of 3 weeks.
- During administration, the patients should be instructed to swallow tablets with water within 30 minutes after meals (breakfast and dinner)
- Daily dose of capecitabine is determined according to the body surface area (BSA), please refer to appendix 5 for the right dose and the number of pills.

Pseudomonas aeruginosa injection (PA-MSHA)

- Manufacturer: Beijing Wanter Bio-pharmaceutical Co., LTD.;
- Properties: milky white liquid, with particles, without sundry;
- Specification: one-time prefilled syringes, with 1 ml/per syringe;
- Storage: 2~8℃ in the absence of light.
- Usage: subcutaneous injection, first dosage of 0.5 ml, then 1 ml/time, every other day (qod).

Precautions:

1) People with a history of allergy should cautiously use it, especially the crowd with a history of multiple drug allergy, who are not suggest to enter the group.

2) A small amount of precipitation may be seen during storage. The refrigerated liquid should be returned to room temperature and fully shaken before using. No block substance or foreign body should be seen.

3) Should not be mixed with other drug. Subcutaneous injection only; intracutaneous injection can cause serious local reactions; injection speed should be as slow as possible.

4) Packed with one-time prefilled syringe; should not use it for several times.

5) After subcutaneous injection, a few of patients may appear the phenomenon such as swelling, and pain, which can be recovered by themselves and do not need special treatment. The second injection should be in the other side. If subcutaneous nodule is seen or patients with severe symptoms, local hot compress is advised to promote drug absorption. Periumbilical and health upper limb can be used for subcutaneous injection in turn.

6) Resting more, drinking more water and keeping warm can reduce adverse reaction. For example, if excluded other causes, fever over 38.5 ℃ can be treated symptomatically, especially physical cooling method. With antipyretic analgesics agents (e.g., indomethacin suppository or emplastrum) the symptomatic treatment can be alleviated quickly.

7) If there is intolerant toxicity, the medication can be reduced to 2 times per week.

8) If the patients appear side effects, such as high fever and chills, clinical nursing should be strengthened, and the specific methods should be proposed by doctors according to the clinical experiences. Antipyretic analgesics agents are suggested to prevent the side effects in advance.

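### The protocol tells sites to make up missed capecitabine doses but not where, and one way of doing so shortens the rest before the next course

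*Protocol*

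**What the plan says.** Section IV of the protocol sets the regimen as "capecitabine 1000 mg/m2 orally twice a day for 2 weeks on, 1 week off". The administration instructions in Section IX repeat it with day numbers: "Capecitabine of 1000 mg/m2 is given twice every day, from the first day to the 14th day in the cycle of 3 weeks".

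Section IX (Xeloda) also covers breaks in treatment. It first allows a delay for toxicity: "Drug administration are allowed to delay for 3 weeks in order to allow the toxicity to recover to baseline levels or grade 0~1". For an interruption it then says that "the later treatment should continue to follow the schedule as planned, and the dose missing due to interruption of treatment should be made up". The next sentence deals with a longer break: "if the rest period extended over the next treatment cycle, capecitabine should be given a full dose of 14 days at restart of treatment".

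The one appendix cited there is described by its purpose: "Please refer to appendix 5 for the standard dose according to body surface area and dose reduction of capecitabine". The appendix is not in the text at hand. Neither that citation nor the second one, for the dose and the number of pills, mentions missed doses.

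**The concern.** The sentence on interruptions gives two instructions: keep to the planned schedule, and make up what was missed. The planned schedule has no free dosing slot in days 1 to 14, so the second instruction needs days that the schedule does not provide. The protocol names no make-up days, no make-up dose and no limit. The restart rule that follows does not help, because it applies only when the rest runs into the next cycle. The gap is the interruption within a cycle.

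What is at stake is patient safety and uniform treatment. Section IX allows delay so that toxicity can settle. If a site places the missed doses in the rest week, a patient who has just been interrupted for toxicity may go into the next course with little or no rest. Another investigator could lengthen the cycle instead, so two patients with the same interruption could be treated differently under the same sentence.

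**Working it through.** **Inputs from the protocol.** The dose is 1000 mg/m2 twice daily, on days 1 to 14 of a 21-day cycle (Sections IV and IX). The rest is therefore 21 − 14 = 7 days.

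**Assumption.** The protocol gives no frequency or length of interruptions. I take m = 2, 4 or 7 missed dosing days as a range.

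**Planned cycle.** There are 14 × 2 = 28 dose slots, all used. The cycle dose is 1000 × 2 × 14 = 28000 mg/m2, or 28000/21 = 1333 mg/m2 per calendar day.

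**Where make-up doses could go.** Doubling up on dosing days would give 4000 instead of 2000 mg/m2 per day and so breaks the fixed dose. With the dose kept, two routes remain.

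(a) *Dose on m of the 7 rest days.*
- Total days off in the cycle: m + (7 − m) = 7, as planned.
- Total dose: 2000 × (14 − m) + 2000 × m = 28000 mg/m2, as planned.
- Rest left before the next course: 7 − m.
- For m = 7, days 15 to 21 (7 days) run into the next days 1 to 14 (14 days), giving at least 7 + 14 = 21 consecutive dosing days after the break, instead of 14.
- More than 7 missed days cannot fit.

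(b) *Complete 14 dosing days, then rest 7.*
- Cycle length: 21 + m days.
- Mean dose: 28000/(21 + m) mg/m2 per calendar day.

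**For comparison, no make-up.** Cycle dose: 2000 × (14 − m) mg/m2.

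| Missed days m | (a) rest days left | (b) cycle length, days | (b) mg/m2 per calendar day | No make-up: mg/m2 in the cycle (share of 28000) |
| --- | --- | --- | --- | --- |
| 2 | 5 | 23 | 1217 | 24000 (86%) |
| 4 | 3 | 25 | 1120 | 20000 (71%) |
| 7 | 0 | 28 | 1000 | 14000 (50%) |

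**Reading the sentences together.** Route (a) departs from the week off in Section IV. Route (b) keeps that week but departs from the three-week cycle in Section IX. Not making up the doses departs from neither. It also agrees with the first half of the disputed sentence and with the restart rule, which asks for a full 14-day course and mentions no additional doses.

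**The case against.** The strongest reply is that this is an unspecified method and not an impossible instruction. Route (b) is coherent. It keeps two weeks on and one week off, and the protocol already lets the calendar slip: Section IX permits a three-week delay, and Section X stops treatment only beyond that. The phrase about later treatment can fairly be read as later cycles run as planned once the interrupted one is complete. This stands. A reader might infer that the two halves of the sentence can never both be followed, and the document does not support that.

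A reader might also infer over-dosing. Route (b) spreads the same dose over more days. Route (a) gives the planned dose and the planned number of days off, so the rest is moved and not lost. What remains is the shorter break immediately before the next course.

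Safeguards also count. Toxicity must recover to baseline or grade 0 to 1, and reduced doses are not raised again (Section IX). Laboratory tests, examination and performance status are checked at the start of every cycle (Section VI.2). Treatment stops for unacceptable adverse events, more than two dose adjustments, a delay beyond three weeks, or the investigator's judgement (Section X). Study procedures stop at once for a serious adverse event (Section XI.4). These reduce the risk but do not tell a site where to put the missed doses.

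Finally, a 'not' may have been lost in translation; one heading in Section VIII is still in Chinese. That is plausible but is an inference. If it is right, the English text gives the opposite of the intended instruction and still needs correcting.

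**Conclusion.** The point holds as a minor one. Section IX orders missed capecitabine doses to be made up without saying how. The order fits poorly with the first half of its own sentence. At the fixed dose it can be carried out only by dosing in the rest week or by lengthening the cycle.

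The consequence of interest arises under rest-week make-up alone: 5, 3 or 0 days of rest before the next course for 2, 4 or 7 missed days and, at 7, at least 21 dosing days in a row after the break. These lengths are assumptions, and how often they would occur is unknown. The patients affected may have been interrupted for toxicity, but the sentence does not restrict itself to that cause.

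The conclusion concerns the English text. The source-language wording and Appendix 5 could not be seen. A reader might go on to infer a bias in PFS or a loss of power. Nothing in the document supports that, and none is claimed.

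**What to change.** Check the source-language text first, looking for a lost 'not'. Then replace the clause with: *Doses missed because of interruption are not made up; resume the planned days 1–14 schedule.*

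If the source text does intend make-up, say instead: *Complete 14 dosing days, then take a full 7-day rest before the next cycle; do not dose during the rest period.*

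Either version is one clause in an amendment and a letter to the site, with no added visits, procedures or patients. The first option lowers the dose in interrupted cycles only, by 14%, 29% or 50% for 2, 4 or 7 missed days (m/14). The second keeps the full course and the full rest, at the price of a cycle of 23, 25 or 28 days.

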**X. Study suspension**

Study suspension refers to the clinical trials that are not over according to the plan stop due to the following reasons. The main purpose is to protect the rights and interests of the subjects, ensure the test quality, and avoid unnecessary economic losses.

- Disease progression;
- Unacceptable adverse events;
- Dose adjustment for more than twice;
- Investigator think it necessary to stop the test of the patients;
- The patients withdraw inform consent;
- The patients delay the treatment for more than 3 weeks;
- Death.

**XI. Process and report of adverse events**

**1. Adverse events**

Adverse events (AEs) refer to the adverse medical events occurred in patient or clinical trial subjects after using a drug, but they may not necessarily have causal relationship with the treatment.

**2. Reporting period of adverse events**

Adverse events occurring between randomization and the last follow-up, no matter related to the research drug or not, should be filled in the case report form. In addition, any adverse incident happens after the reporting period, if being estimated associated with the research drug, the researcher also should report it as adverse events.

**3. Serious adverse event (SAE)**

Adverse events in accordance with one or more of the following criteria are defined as serious adverse events:

- Death;
- Life-threatening;
- Events that may result in hospitalization or prolong the hospital stay
- Permanent or serious disability;
- Congenital malformations/defect, important medical events.

**4. Report pathways of serious adverse events**

For all serious adverse events, the patients must stop study procedure immediately, and should be given corresponding protection measures. Researchers must report the sponsor the serious adverse events within 24h on telephone or fax. The researchers should track the serious adverse event until it is solved. Relevant medical documents shall be recorded in the original file, including laboratory examination results report (such as X-ray, ECG, etc.).

**5. Records and reports**

For the adverse events during the test, onset time, symptoms, degree, duration, treatment measures and outcome, etc., should be recorded in case report form. And their relevance to test drugs should be evaluated, and recorded by the researchers in detail. The researcher should sign and date the report. Severity of adverse events will be classified according to the NCI CTC3.0 version. For each symptom, it should be reported the highest classification of the adverse events since the last follow-up.

Relationship between adverse events and the experimental drugs

|  | Certainly relevant | Very possible to be relevant | May be relevant | Suspect | Impossible to be relevant |
| --- | --- | --- | --- | --- | --- |
| With the reasonable time sequence after medication | + | + | + | + | — |
| Known reaction types | + | + | + | — | — |
| Effect relieved or disappeared after removing the drugs | + | + | ± | ± | — |
| Effects appear again when administrate the drugs again | + | ？ | ？ | ？ | — |
| Cannot explain with the patients’ disease | + | + | — | ± | — |

**XII. Sample size**

It is expected that the PFS will be prolonged from 4.2 months with monotherapy of Xeloda to 5.7 months after combined with pseudomonas aeruginosa injection. So according to a=0.05 and power of 85%, the needed sample size is 88 cases; 96 patients were required in consideration of 10 % expulsion rate.

**XIII. Data processing**

**1. Requirement of researchers to fill data**

1) All of the patients who have signed an informed consent form and have been included in the experiment through screening, should record all of the items of the case report form carefully and in detail, no blank or omission is allowed (fill a cross in the blank space without any record);

2) All of the data in case report form should be checked with the medical data of the patients, to ensure flawless;

3) Case report form is used as original data, so any correction can only made by a line and marginal note of the new data, sign of the researchers and the data;

5) Data significantly higher or beyond the acceptable range in clinical must be verified, and explained by researchers;

**2. Requirement of CRA (clinical researcher associate) to monitor data**

1) CRA should regularly examine whether the subjects of each test center are informed and agreed and the screening and inclusion situations;

2) To confirm the case report form is filled correctly and is consistent with the original data;

3) All the errors or omissions are correct or noted, signed and dated by the researchers;

4) Dose change, treatment changes, drug combination, periodic disease, etc. of each subject, need to be identified and recorded;

5) To verify the selected participants who drop out from the test or are failed to follow up, and the situations should be given in the case report forms;

6) To confirm all the adverse events are recorded, and the serious adverse events are recorded are made a report;

7) To confirm whether the drugs are supplied, stored, distributed, returned and recorded in accordance with the relevant provision;

8) Each selected case is required to complete the CRF. And the original completed CRF belongs to Beijing Wanter Bio-pharmaceutical Co., LTD. The original completed CRF should not be provided to the third parties in any form without the written consent of the company, unless the requirements from State Drug Administration (SFDA);

9) CRF is filled by the researchers, and each selected cases must complete the CRF. The finished CRF should be examined by the CRA. The first page is transferred to the data statistics unit for data entry and management work; the second to the sponsor to be archived; and the first page is given to the clinical pharmacology base of each center to be archived.

**3. Traceability of the data, filling and transfer of the CRF**

The original records are medical records of the research and need to be properly kept. Case report form is from the medical records, and is filled by the researchers. Each selected cases must complete the CRF. The finished CRF should be examined by the CRA. The first page is transferred to the data statistics unit for data entry and management work; after transfer, the CRF cannot be corrected.

**4. Data entry and correction**

Data administrators of the statistical unit are in charge of the data entry and management. Epidata software is adopted to establish the special database for data entry and management. In order to guarantee the accuracy of the data, double entry and correction should be conducted by two data administrators independently.

For questions exist in the CRFs, data administrator will fill out the DRQ (data ready queue), and ask the researchers through CRF. The researchers should answer as soon as possible. Then data administrators would modify the data according to the researcher’s answer, confirm and entry the data. They are allowed to send DRQ again if necessary.

**5. Data locking**

When the data are reviewed and the established database is confirmed to be correct. The data will be locked by the principal investigator, the sponsor, statistical analysts and the pharmaceutical supervisory mangers. After locking the data file cannot be changed again. Problems found after locking, can be revised in the statistical analysis program after confirmation.

**XIV Statistical analysis**

Professional statisticians are responsible for statistical analysis, and participate in the whole process from test design, implementation to the analysis and summary. Statistical analysis plan is established after the completion of test protocol and case report form, and is made necessary changes in the test process according to the needs. Statistical analysis plans should be finished before data locking. And after the statistical data analysis is completed, statistical analysis report is provided.

1. **Data set analsis**

**1) FUll Analysis Set-FAS**: refers to the sets of eligible cases and off cases, but does not include excluded cases.

2) **Per-Protocol population** (PP): refers to the sets of cases that meet eligibility criteria and complete the treatment, namely the cases that are in accordance with the test protocol and with good adherence, don’t use banned drugs, and complete the CRF.

3) **Safety set:** the cases at least receive one time of treatment.

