**3. Analysis method**

1) Measurement data: t test, paired t test, rank-sum test, paired rank-sum test and other methods;

2) Enumeration data: Fisher’s exact test, etc.; rank-sum test is adopted for ranked data.

3) Curative effect analysis: CMH chi-square test or logistic regression is used for enumeration data; variance analysis or rank-sum test is adopted for measurement data according to the characteristics of data; Kaplan-meier method or Cos regression is adopted for survival data.

4) FAS analysis and PP analysis: the two analyses are performed at the same time for the main curative effect indexes.

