**4. Statistical expression**

Bilateral inspection is adopted generally, P less than or equal to 0.05 will be considered a statistically significant discrimination.

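### The per-protocol set is defined by completing a treatment that has no fixed end, so early PFS events can remove patients from a set used to test PFS against a historical 4.2 months

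*Protocol*

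**What the plan says.** Three analysis sets are defined in Protocol section XIV.1.

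- The FAS "refers to the sets of eligible cases and off cases, but does not include excluded cases". The protocol does not define which cases count as excluded.
- The PP set "refers to the sets of cases that meet eligibility criteria and complete the treatment". The same sentence then explains this as following the protocol with good adherence, using no banned drugs and having a complete case report form.
- The safety set is everyone treated at least once.

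For FAS and PP, section XIV.3 item 4 says that "the two analyses are performed at the same time for the main curative effect indexes". The primary endpoint in section VIII is PFS. Neither set is named as the one that decides.

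Two other sections bear on what completion means. Section IV says: "The patient may continue treatment until unacceptable toxicities, disease progression". Section X lists disease progression, unacceptable adverse events, withdrawal of consent and death among the reasons for a stop that was not according to plan.

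The trial is single-arm and open-label (section II). Section XII expects that "PFS will be prolonged from 4.2 months with monotherapy of Xeloda" "to 5.7 months after combined with pseudomonas aeruginosa injection".

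**The concern.** Treatment that runs until progression or toxicity has no course to complete. If section X is used to decide who completed, a patient who progresses or dies early did not, and leaves the PP set. Progression and death are ordinarily the events that make up PFS, so the primary outcome would decide who belongs to a set in which that outcome is tested.

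In a randomised trial a control arm would share some of this selection. Here the comparison is with a fixed historical figure, so any lengthening of PFS through selection passes straight into the apparent drug effect. The planned gain is 5.7 − 4.2 = 1.5 months, which is small enough for selection of this kind to matter.

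**Working it through.** **The plan's own figure.** Section XII states that "according to a=0.05 and power of 85%, the needed sample size is 88 cases", and section XIV.4 says "Bilateral inspection is adopted generally, P less than or equal to 0.05". No formula is given. A one-sample exponential test on the median scale, with all events observed, gives

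n = ((1.960 × 4.2 + 1.036 × 5.7) / 1.5)² = (14.14 / 1.5)² ≈ 88.9,

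so 89 against the stated 88. Allowing 10% for removals, 88 × 1.1 = 96.8, close to the stated 96. The planning is therefore consistent with a one-sample comparison against 4.2 months, which is the comparison used below.

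**Inputs.** The true median is 4.2 months (no drug effect) and 96 patients are enrolled. Cycles last three weeks (section IX), so one cycle is 21 / 30.44 = 0.69 months and two cycles are 1.38 months. The first scheduled tumour assessment falls at two cycles (section V.1). Two things are assumed because the protocol does not give them: exponential PFS, and a cut-off L before which a share p of patients with an event is dropped as not having completed.

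**Median of the retained patients.** The share with an event before L is F = 1 − 2^(−L/4.2), which is 10.8% at one cycle and 20.4% at two. As long as it lies beyond L, the retained median is

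4.2 − 4.2 × log2(1 − pF).

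For example, at two cycles with p = 0.5: 4.2 − 4.2 × log2(1 − 0.102) = 4.85. With p = 1 the formula reduces to 4.2 + L.

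**False-positive rate.** One-sample log-rank test against 4.2 months, upper tail z > 1.96, 20,000 simulated trials, no censoring:

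| Cut-off | Share of earlier events dropped | Patients lost | Median (months) | Rejects |
| --- | --- | --- | --- | --- |
| none | 0% | 0% | 4.20 | 2% |
| one cycle | 25% | 2.7% | 4.37 | 3% |
| one cycle | 100% | 10.8% | 4.89 | 13% |
| two cycles | 10% | 2.0% | 4.32 | 3% |
| two cycles | 25% | 5.1% | 4.52 | 5% |
| two cycles | 50% | 10.2% | 4.85 | 11% |
| two cycles | 100% | 20.4% | 5.58 | 40% |

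A different test (log of the estimated median, with an assumed 18-month accrual and a data cut at 24 months) gives 15% and 47% for the two 100% rows, so the order of magnitude does not depend on the test.

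**The FAS.** If the whole 10% allowance were spent on the earliest progressors, the median would be 4.2 − 4.2 × log2(0.9) = 4.84 months. In the second simulation, dropping the earliest 8 or 10 of 96 gives 11% or 16% false positives. Dropping 8 at random leaves the rate at 1.9%, so only exclusion related to outcome does harm.

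**The case against.** The strongest reply is that the PP sentence goes on to explain itself in terms of adherence, banned drugs and a complete case report form. That is an ordinary PP definition, and a patient treated until progression has done what section IV asks. This stands as a possible reading, and under it the bias is smaller than any of the upper-bound figures. It does not remove the completion condition from the text, and section X points the other way.

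The second reply concerns size. With the first scan at two cycles, most radiological progression in that window would be found after the patient had received both cycles. Only deaths and clinical progressions before the scan would be lost. This also stands, and is why the 100% rows are upper bounds and the 10% to 50% rows are shown beside them.

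A reader might infer three stronger things that the documents do not support.

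- That the FAS rule can also create the target effect. The FAS keeps patients who went off study, its excluded cases may simply be ineligible enrolments, and even the worst use of the 10% allowance reaches about 4.8 months, not 5.7.
- That treated patients will be dropped once results are known. No section provides for this.
- That two sets give two chances to succeed. Section XIV.3 says only that both analyses are done; it does not say that success in either suffices. Running both is common sensitivity practice.

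A later SAP may define terms and name the deciding set, and its absence here is no fault. The completion condition is different: this protocol states it, and a SAP would have to depart from the protocol to repair it.

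**Conclusion.** The point holds for the PP definition. Sections IV, X and XIV.1 do not agree on what completing treatment means, and one available reading selects patients on the primary outcome in a single-arm trial.

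The size depends on that reading. The upper bound is a median of 4.9 months and 13% false positives (one cycle), or 5.6 months and 40% (two cycles), against a nominal 2.5% in the upper tail. With 10% to 50% of the events before two cycles dropped, it is about 4.3 to 4.9 months and 3% to 11%. It is smaller still if treatment to progression counts as completion. All of this rests on exponential PFS and on cut-offs and dropped shares that the protocol does not give.

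The bare claim that the PP rule produces the whole 1.5-month gain would go too far: it comes close only when every event before two cycles is dropped. The undefined exclusions from the FAS are a secondary concern.

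**What to change.** - Name all enrolled patients who received at least one dose, which is the existing safety set, as the deciding set for PFS. Count early progressions and deaths as events.
- Label the PP analysis supportive. Delete the completion condition and define PP by eligibility and a list of major deviations settled before data lock.
- Reconcile sections IV, X and XIV.1 on what completion of treatment means.

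This changes wording in the protocol and SAP only, with no extra patients or data. The downside is that the reported PFS may be shorter than it would be in the PP set.
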